## Flow Chart

| Items                     | Screening Period                 |                                  | Neoadjuvant Treatment Period |            |            |            |                         |            |            |            |            | Surgery                       |                              | Adjuvant Treatment Period |            |            |
|---------------------------|----------------------------------|----------------------------------|------------------------------|------------|------------|------------|-------------------------|------------|------------|------------|------------|-------------------------------|------------------------------|---------------------------|------------|------------|
|                           | Within 2 weeks before enrollment | Within 1 weeks before enrollment | Cycle 1                      | Cycle 2    |            | Cycle 3    |                         | Cycle 4    |            | Cycle 5    |            | Within 1 weeks before surgery | Within 1 weeks after surgery | Cycle 1                   |            | Cycles 2-6 |
|                           |                                  |                                  | Day 7 (±3)                   | Day 1 (±3) | Day 7 (±3) | Day 1 (±3) | Day 7 (±3)  | Day 1 (±3) | Day 7 (±3) | Day 1 (±3) | Day 7 (±3) |                               |                              | Day 1 (±3)                | Day 7 (±3) | Day 1 (±3) |
| Baseline characters       |                                  |                                  |                              |            |            |            |                         |            |            |            |            |                               |                              |                           |            |            |
| Informed consent          | x                                |                                  |                              |            |            |            |                         |            |            |            |            |                               |                              |                           |            |            |
| Demographics characters   | x                                |                                  |                              |            |            |            |                         |            |            |            |            |                               |                              |                           |            |            |
| History of other diseases | x                                |                                  |                              |            |            |            |                         |            |            |            |            |                               |                              |                           |            |            |
| Vital signs               |                                  | x                                |                              | x          |            | x          |                         | x          |            | x          |            | x                             | x                            | x                         |            | x          |
| Physical examination      |                                  | x                                |                              | x          |            | x          |                         | x          |            | x          |            | x                             | x                            | x                         |            | x          |
| Laboratory tests          |                                  |                                  |                              |            |            |            |                         |            |            |            |            |                               |                              |                           |            |            |
| Peripheral blood routine  |                                  | x                                | x                            | x          | x          | x          | x                       | x          | x          | x          | x          | x                             | x                            | x                         | x          | x          |
| Urinary routine           |                                  | x                                |                              | x          |            | x          |                         | x          |            | x          |            | x                             |                              | x                         |            | x          |
| Stool routine             |                                  | x                                |                              | x          |            | x          |                         | x          |            | x          |            | x                             |                              | x                         |            | x          |
| Blood chemistry           |                                  | x                                | x                            | x          | x          | x          | x                       | x          | x          | x          | x          | x                             | x                            | x                         | x          | x          |
| Coagulation tests         |                                  | x                                |                              | x          |            | x          |                         | x          |            | x          |            | x                             |                              | x                         |            | x          |
| Tumor markers             |                                  | x                                |                              | x          |            | x          |                         | x          |            | x          |            | x                             |                              | x                         |            | x          |

|                                  |   |   |                     |   |   |   |   |   |   |   |   |   |   |   |   |   |
|----------------------------------|---|---|---------------------|---|---|---|---|---|---|---|---|---|---|---|---|---|
| Tumor sample collection          |   |   |                     |   |   |   |   |   |   |   |   |   | x |   |   |   |
| Gastroscopy                      |   | x |                     |   |   |   |   |   |   |   |   |   |   |   |   |   |
| Electrocardiograms               |   | x |                     | x |   | x |   | x |   | x |   | x |   | x |   | x |
| Pregnancy tests                  |   | x |                     |   |   |   |   |   |   |   |   |   |   |   |   |   |
| Radiologic assessments           |   |   |                     |   |   |   |   |   |   |   |   |   |   |   |   |   |
| Imaging examination † | x |   | Every 2 cycles (±7) |   |   |   |   |   |   |   |   |   |   |   |   | x |
| Other assessments                |   |   |                     |   |   |   |   |   |   |   |   |   |   |   |   |   |
| ECOG score                       |   | x |                     | x |   | x |   | x |   | x |   | x | x | x |   | x |
| Blood pressure monitoring        |   | x | x                   | x | x | x | x | x | x | x | x | x | x | x | x | x |
| Adverse events                   |   |   | x                   | x | x | x | x | x | x | x | x | x | x | x | x | x |
| Others                           |   |   |                     |   |   |   |   |   |   |   |   |   |   |   |   |   |
| Concomitant drugs                |   |   | x                   | x | x | x | x | x | x | x | x | x | x | x | x | x |
| Drug compliance                  |   |   |                     | x |   | x |   | x |   | x |   |   |   | x |   | x |

23 **Abbreviations**

| Abbreviations | Full names                                                    |
|----------------------|----------------------------------------------------------------------|
| AE                   | Adverse events                                                       |
| AGC                  | Advanced gastric cancer                                              |
| AKP                  | Alkaline phosphatase                                                 |
| ALB                  | Albumin                                                              |
| ALT                  | Alanine aminotransferase                                             |
| ANC                  | Absolute neutrophil count                                            |
| APTT                 | Activated partial thromboplastin time                                |
| AST                  | Aspartate aminotransferase                                           |
| Bid                  | Bis in die                                                           |
| BIL                  | Bilirubin                                                            |
| BSE                  | Body surface area                                                    |
| BUN                  | Blood urea nitrogen                                                  |
| CFDA                 | China Food and Drug Administration                                   |
| CI                   | Confidence interval                                                  |
| Cr                   | Creatinine                                                           |
| CR                   | Complete response                                                    |
| CRF                  | Case Report Form                                                     |
| CT                   | Computed tomography                                                  |
| DFS                  | Disease-free survival                                                |
| DRQ                  | Data Request Question                                                |
| ECOG PS score        | Eastern Cooperative Oncology Group scale
Performance status score |
| FAS                  | Full Analysis Set                                                    |
| Fbg                  | Fibrinogen                                                           |
| GCP                  | Good Clinical Practice                                               |

| Abbreviations | Full names                                       |
|----------------------|---------------------------------------------------------|
| Hb                   | Hemoglobin                                              |
| ICF                  | Informed consent form                                   |
| INR                  | International Normalized Ratio                          |
| IRB                  | Institutional Review Board                              |
| LDH                  | Lactate dehydrogenase                                   |
| MRI                  | Magnetic resonance imagin                               |
| NCI-CTC              | National Cancer Institute - Common Terminology Criteria |
| OS                   | Overall survival                                        |
| PET                  | Positron emission tomography                            |
| PD                   | Progressive Disease                                     |
| PLT                  | Platelet                                                |
| PR                   | Partial Response                                        |
| PT                   | Prothrombin time                                        |
| Qd                   | Quaque die                                              |
| Qod                  | Quaque secundo die                                      |
| QoL                  | Quality of Life                                         |
| RBC                  | Red blood cells                                         |
| RECIST               | Response Evaluation Criteria in Solid Tumors            |
| SAE                  | Severe adverse events                                   |
| SD                   | Stable Disease                                          |
| SOC                  | System organ classification                             |
| TBIL                 | Total bilirubin                                         |
| TP                   | Total protein                                           |
| TT                   | Thrombin time                                           |
| ULN                  | Upper limit of normal                                   |
| VEGFR                | Vascular endothelial growth factor receptor             |
| WBC                  | White blood cells                                       |
| γ-GT                 | Glutamyl transferase                                    |

## 1. Background

There were over 1,000,000 new cases and an estimated 783,000 deaths caused by gastric cancer in 2018, making it the fifth most frequently diagnosed cancer and the third leading cause of cancer death [1]. Endoscopic or surgical resection is curative in most early gastric cancers, with a 5-year overall survival (OS) rate greater than 90% [2]. In contrast, prognosis remains poor for locally AGC even after the complete dissection of the primary tumors and regional lymph nodes [3]. Thus, multimodal treatments have been proposed to prolong the survival period. Since the MAGIC trial published in 2006 first demonstrated that perioperative chemotherapy (ECF) could increase the 5-year OS rate from 23% to 36% compared with surgery alone ( $P = 0.009$ ) [4], systemic chemotherapy has become the standard treatment for locally AGC [5]. In Asia, oral fluoropyrimidines (e.g., S-1 or capecitabine) plus oxaliplatin is considered a first-line regimen [6-7]. However, chemotherapy was reported to be less effective against gastric cancer than against other solid malignancies because of the heterogeneity of tumors [8-9]. Therefore, new treatment options showing promising efficacy and acceptable safety profiles are urgently needed.

In the past decade, several clinical trials have been performed to investigate molecular targeted therapy for AGC, but few molecular agents have shown promising activity [10-13]. The ToGA trial demonstrated that trastuzumab with cisplatin and capecitabine or 5-FU (XP/FP) was associated with improved OS for HER2-positive advanced G/GEJ cancer [10]. Unfortunately, only a small percentage of patients (approximately 20%) are ideal candidates for HER-2 targeted therapy [10, 14-15]. Another well-established target is vascular endothelial growth factor (VEGF). VEGF is one of the most potent angiogenic factors and is a signaling molecule secreted by many solid tumors [16-17]. Since high VEGF expression is one of the characteristic features of gastric carcinomas, targeting VEGF is therefore considered a promising therapeutic strategy.

Apatinib, a novel receptor tyrosine kinase inhibitor selectively targeting VEGFR-2, strongly inhibited VEGF-mediated endothelial cell migration, proliferation, and tumor microvascular density [18]. A phase III study showed that apatinib improved OS and progression-free survival (PFS) in patients with chemotherapy-refractory advanced or metastatic adenocarcinoma of the stomach or gastroesophageal junction (GEJ) when compared with placebo [19].

Neoadjuvant chemotherapy could decrease the tumor stage, increase the R0 resection rate and the survival benefits for AGC patients [20-21]. However, rare evidence supports the utility of apatinib combined with chemotherapy in neoadjuvant treatment. Thus, a multicenter, prospective study was conducted to investigate the efficacy and safety of apatinib plus SOX for the neoadjuvant treatment of locally AGC.

## **2. Objective**

### **2.1 Primary End Point**

R0 resection rate

### **2.2 Secondary End Point**

Pathological / radiologic response rate, toxicity, and surgical outcome

## **3. Research Pattern and Design**

### **3.1 Research Pattern**

This is a multicenter, single-arm, prospective, Phase 2 study.

### **3.2 Criteria for Study Population**

#### **3.2.1 Inclusion criteria**

- (1) Age from 18 to 75 years
- (2) Primary gastric adenocarcinoma (papillary, tubular, mucinous, signet ring cell, or poorly differentiated) confirmed pathologically by endoscopic biopsy
- (3) cT2-4/N+M0 at preoperative evaluation according to the American Joint Committee on Cancer (AJCC) Cancer Staging Manual Seventh Edition
- (4) No distant metastasis is observed. And the spleen, pancreas or other adjacent organs are not involved by the tumor.
- (5) Performance status of 0 to 2 on Eastern Cooperative Oncology Group scale (ECOG)

(6) Without previous surgical, chemotherapy, radiotherapy, immunotherapy, or targeted therapy for gastric cancer.

(7) Estimate life is equal or more than 3 months

(8) No serious heart, lung, liver dysfunction; no jaundice or obstruction of the digestive tract; no acute infection

(9) The main organ function is normal, and meet the following criteria:

blood routine examination (No blood transfusion within 14 days)

HB $\geq$ 100g/L,

WBC $\geq$ 3.5 $\times$ 10^9/L,

ANC $\geq$ 1.5 $\times$ 10^9/L,

PLT $\geq$ 100 $\times$ 10^9/L;

blood biochemical examination

BIL $<$ 1.5 Upper Limit Of Normal (ULN) ,

ALT and AST $<$ 2.5ULN, GGT $\leq$ 1.5 $\times$ ULT;

Cr $\leq$ 1ULN, creatinine clearance  $>$  60ml/min (Cockcroft-Gault formula)

(10) Written informed consent

### 3.2.2 Exclusion criteria

(1) Pregnant and lactating women

(2) Severe mental disorder

(3) History of previous upper abdominal surgery (except for laparoscopic cholecystectomy)

(4) History of previous chemotherapy or radiotherapy

(5) History of other malignant disease within the past 5 years

(6) History of unstable angina or myocardial infarction within the past 6 months

(7) History of cerebrovascular accident within the past 6 months

(8) History of continuous systematic administration of corticosteroids within 1 month

(9) Emergency surgery due to complication (bleeding, obstruction or perforation) caused by gastric cancer

(10) Patients with a clear tendency of gastrointestinal bleeding, such as: active ulceration, fecal occult blood test(++). History of hematemesis and melena

within 2 months, coagulation disorders (INR>1.5、APTT>1.5 ULN).

(11) Positive urinary protein(uric albumen check(++),or 24-hour urinary protein content>1.0g)

(12) Factors affecting oral administration, such as dysphagia, uncontrollable nausea and vomiting, chronic diarrhea, and intestinal obstruction

(13) Drug allergy to experimental medicine

### 3.2.3 Rejection criteria

(1) Do not meet the inclusion criteria and meets the exclusion criteria;

(2) Simultaneous application of CFDA-approved modern Chinese medicine or immunomodulators for the treatment of gastric cancer;

(3) Radiation therapy or other local treatments during the study periods;

(4) Incomplete data;

(5) Do not take medicine according to the dosage, method, and treatment prescribed in the protocol.

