#### **4.3 Preoperative evaluation and surgical period**

After completing neoadjuvant treatment, peripheral blood routine, blood biochemistry, stool routine, urine routine, 12-lead electrocardiograms, tumor markers, and coagulation function should be performed to evaluate the efficacy as well as the patients' physical condition. Without clear surgical contraindications and with the patients' consent, surgery will be performed 2–4 weeks later. If disease progresses, radiochemotherapy or salvage surgery is recommended.

- Record the results of peripheral blood routine, blood biochemistry, stool routine, urine routine, 12-lead electrocardiograms, tumor markers, and coagulation tests which are performed 7 days before and after the surgery;

- Retain pathological tissue specimens after surgery;
- Record the reasons for not surgery;
- Record operation time, blood loss, and intraoperative complications (e.g. major bleeding);
- Record postoperative complications and management;
- Record pathological type, number of lymph nodes harvested and metastasis;
- Record postoperative hospital days.

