### **● Efficacy**

#### **- Primary Efficacy Measures**

Calculate the R0 resection rate with 95% confidence interval (CI).

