#### 1. General Considerations for Dose Adjustment

- For AEs present at baseline, the dose can be adjusted according to the change in grades. For example, if grade 1 weakness at baseline progresses to grade 2 during treatment, the dose can be adjusted as the presence of a grade 1 toxicity.
- There is no need to reduce the dose or discontinue the treatment with the presence of the toxicities which are unlikely to develop into severe events (such as hair loss, appetite changes, etc.) occur. Additionally, there is no need to reduce the dose or discontinue the treatment with the presence of anemia (non-hemolytic) because it can be improved by transfusion.
- When different grades of toxicities occur simultaneously, dose reduction should be taken according to the most severe of them.
- During treatment, if all study drugs need to be delayed or discontinued for more than six weeks, the patient will withdraw from the study. If only one drug is discontinued, the study still proceeds.
- If a patient develop a grade 3 or higher non-hematological AE, it can be discussed with the sponsor whether to reduce the dose or not.

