#### 3.2 Principles for Dose Adjustment and Interruption

- Dose reductions are allowed in the presence of grade 3 treatment-related toxicities.
- Among non-hematological toxicities, there is no need to reduce the dose or discontinue the treatment in the presence of manageable nausea, vomiting, hair loss, fever with a defined cause (such as infection or tumor), and grade 3/4 elevated alkaline phosphatase (AKP).
- Dose reductions are allowed up to twice. Treatment interruption is allowed for no more than 14 days (cumulatively) and no more than two times in each cycle. Dose re-escalation is not permitted.
- Treatment interruption is first performed during each cycle. Then dose reduction can be performed when the subject is still intolerant.
- Special AEs: Once hypertension crisis, cerebral hemorrhage, grade 2 or higher pulmonary hemorrhage, grade 3 or higher other bleeding, arterial thrombosis, grade 4 venous thrombosis, leukoencephalopathy syndrome, or gastrointestinal perforation occurs, immediately discontinue the treatment and perform active symptomatic treatment; the subject then withdraw from the study.

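### Rejection and withdrawal rules triggered after enrolment conflict with the progression plan, the FAS and the promised follow-up, so treatment failures can leave the R0 denominator or lose outcome data

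*Protocol*

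**What the plan says.** The primary endpoint is the "R0 resection rate" (section 2.1). Section 6.2, Statistical Analysis, asks for this rate with a 95% confidence interval and names no denominator.

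Section 3.2.3, repeated in the synopsis, lists five rejection criteria. The first concerns eligibility. The second is concurrent use of certain Chinese medicines or immunomodulators. The others are "Radiation therapy or other local treatments during the study periods", "Incomplete data" and "Do not take medicine according to the dosage, method, and treatment prescribed in the protocol". The list stands under the criteria for the study population, apart from the reasons for stopping treatment in section 3.2.4.

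Section 4.3 says: "If disease progresses, radiochemotherapy or salvage surgery is recommended".

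Section 6.2, Definitions of Analysis Sets, puts in the FAS every patient with one or more neoadjuvant cycles. The PPS requires adherence, no prohibited drugs, surgery and a completed case report form. Efficacy is to be analysed in both sets. The section does not mention rejection or withdrawal.

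Appendix 5, part 1, covers a break of all study drugs beyond six weeks: "the patient will withdraw from the study". Part 3.2 covers a list of special adverse events, among them gastrointestinal perforation, serious bleeding and arterial thrombosis: "the subject then withdraw from the study". Section 3.4 promises every participant at least five years of follow-up, and section 4.5 places patients in scheduled follow-up after the last drug.

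**The concern.** Rejection criteria 2 to 5 rest largely on what happens after enrolment, and those events are related to outcome. A patient who progresses, tolerates treatment badly or misses assessments is less likely to reach an R0 resection. Nothing in section 3.2.3 limits the criteria to the PPS, so one analyst could exclude progressors under 3.2.3 and another could keep them under the FAS definition, each citing the protocol.

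Withdrawal raises a second problem. If a patient leaves the study after a perforation or a major bleed, surgery, R0 status, recurrence and death may go unrecorded. The FAS definition keeps that patient in the count but does not supply the outcome, and the resulting gap is itself a listed ground for rejection.

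With about 50 patients and no control arm, a few removed failures move the primary estimate, and no comparison group shares the shift.

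**Working it through.** **1. Rejection against the progression plan.** Section 3.2.3 rejects for any radiation in the study period and writes no exception. Section 4.3 recommends radiochemotherapy as one of two options at progression. A progressor who receives it follows 4.3 and meets criterion 3. The two passages conflict.

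**2. Rejection against the analysis sets.** There are two readings.
- Rejection means only exclusion from the PPS. It then agrees with the FAS definition, but 3.2.3 does not say so.
- Rejection means removal from the study population, as its place in section 3.2 suggests. It then contradicts the FAS definition.

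The protocol does not choose between them, and it does not say whether FAS or PPS carries the primary result.

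**3. Withdrawal against follow-up.** Appendix 5 uses withdrawal from the study where section 3.2.4 speaks of stopping treatment. Sections 3.4 and 4.5 follow all patients after drug ends. Both cannot hold for the same patient.

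**4. Size if failures are removed.** The protocol gives no R0 rate to reproduce, so this is an illustration.

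Inputs:
- n = 50, the planned sample size (synopsis).
- x = number with R0 resection: assumed.
- k = number of failures removed: assumed.

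Formulas:
- Failures kept: x/50. Failures removed: x/(50 − k).
- Shift = x/(50 − k) − x/50 = x·k / [50·(50 − k)].
- Exact (Clopper-Pearson) 95% interval for x out of m: lower limit is the 0.025 quantile of Beta(x, m − x + 1); upper limit is the 0.975 quantile of Beta(x + 1, m − x).

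With x = 40:

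| Failures removed | R0 rate | Exact 95% CI | Shift |
|---|---|---|---|
| 0 | 40/50 = 80.0% | 66.3–90.0 | 0 |
| 2 | 40/48 = 83.3% | 69.8–92.5 | 40·2/(50·48) = 3.3 points |
| 5 | 40/45 = 88.9% | 75.9–96.3 | 40·5/(50·45) = 8.9 points |

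Over x = 30, 35, 40 and 45, removing two failures shifts the rate by 2.5 to 3.8 points, and removing five shifts it by 6.7 to 10.0 points. The lower ends come from x = 30: 30·2/(50·48) = 2.5 and 30·5/(50·45) = 6.7. The upper ends come from x = 45: 45·2/(50·48) = 3.75 and 45·5/(50·45) = 10.0.

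If the FAS is applied as written, with every treated patient in the denominator, k = 0 and the shift is zero.

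**5. Missing outcomes within the FAS.** If k patients withdrawn without R0 would in truth be failures, an available-case analysis gives the same x/(50 − k). If some of them had an R0 resection after withdrawal that was never recorded, counting them as not R0 understates the rate. Only continued follow-up removes both errors.

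**The case against.** The strongest reply is that the FAS already settles the matter. It keeps every patient with one or more cycles, contains no exclusion for rejection or withdrawal, and must be used for efficacy. Criteria 2 to 5 also closely resemble the PPS conditions, so reading them as PPS exclusions is natural. Progressors without surgery and patients with incomplete forms are outside the PPS by its own definition, so there the rejection list adds little. Sections 3.4 and 4.5 can be read as keeping withdrawn patients under observation, and section 4.3 requires the reason for no surgery to be recorded.

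Much of this stands. A reader might infer that treatment failures are deleted from the primary analysis; no passage says so, and the FAS definition points the other way. A reader might also take severe toxicity for a rejection criterion. It is not: section 3.2.4 makes intolerable toxicity a reason to stop treatment, and Appendix 5 withdraws patients only for the listed events or the long break. Nor are all the criteria strictly post-treatment, since data can be incomplete at screening. Loss of outcome data after withdrawal is a risk of the wording, not a stated end to follow-up.

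What the reply does not remove is the conflict between stated rules. Section 3.2.3 is not tied to the PPS, criterion 3 has no exception for section 4.3, no set is primary for R0, and Appendix 5 says study where it could have said treatment. A statistical analysis plan could clarify the denominator, but it cannot recover outcomes that were not collected.

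**Conclusion.** The point holds as a conflict between stated rules. Sections 3.2.3 and 4.3 contradict each other on radiation at progression. Section 3.2.3 contradicts the FAS definition if rejection means removal from the study population. Appendix 5 contradicts the follow-up in sections 3.4 and 4.5. As a result, treatment failures can be removed from the R0 denominator, or can lose outcome data after serious toxicity.

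The size is unknown. It is zero in the FAS denominator if that definition is applied as written. Otherwise it is about 2.5 to 3.8 points for two removed failures and 6.7 to 10.0 points for five, under assumed R0 counts of 30 to 45 out of 50. These figures show sensitivity and do not predict the bias; the documents do not support a claim that R0, response or survival will be inflated by any given amount.

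**What to change.** - **Section 3.2.3 and synopsis:** reconcile them with section 4.3 and the analysis sets. State that the post-enrolment criteria are grounds for exclusion from the PPS only. State also that no patient with one or more cycles leaves the FAS or the safety set because of incomplete data, adherence or later therapy.
- **Section 6.2:** name the FAS as primary for R0, and count patients without a documented R0 resection as not R0.
- **Appendix 5, parts 1 and 3.2:** separate stopping study drug from leaving the study. Patients who stop drug under these rules stay in the scheduled follow-up for surgery, R0 status, safety, recurrence and survival unless they withdraw consent.

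The rules for when drug is stopped, and the treatment offered at progression, are not altered by this. The cost is a wording amendment and continued follow-up of what should be a few patients at visits that section 4.5 already schedules.
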